**Trial Duration:**

- July 2004 to January 2005

**Total budget:**

- The approximate budget of the proposal is US$ 199 355,91

**STUDY OUTLINE**

**Rationale**

- In most of the Soudano-Sahelian zone, the burden of malaria is primarily among children between one and four years of age
- In a trial conducted in Niakhar, rural Senegal, in 2002, seasonal intermittent preventive treatment in children was found to have a marked impact on the incidence of clinical malaria (86% reduction of first clinical episode with more than 3000 parasites per micro litre)
- Results of a study implemented in the same cohort in 2003 showed the no rebound effect
- However, preliminary analysis suggests that although the children who received sIPT had a substantially lower prevalence of parasitaemia at the end of the transmission season than the control children there was a selection of parasites with molecular markers that are linked to resistance to pyrimethamine in the children who had received the intervention (three doses of SP despite the concurrent administration of one dose of artesunate.
- Because of the potential of a SP/one dose of artesunate regimen to select for pyrimethamine resistance, we have decided to explore alternative regimens for sIPT.

**Aim:**

- To improve control of malaria in the Soudano-Sahelian zone and to reduce child morbidity, by determining the best drug combination for seasonal intermittent preventive treatment in children (sIPT).

**General Objective:**

- To assess to what extent using different drug regimens can prevent morbidity from malaria in rural Senegal.

**Specific Objective:**

- To compare the efficacy, safety and effect on drug resistance of artesunate plus Sulfadoxine Pyrimethamine (SP), artesunate plus amodiaquine and Lapdap alone on malaria morbidity when used for sIPT.

**Study site:**

- Niakhar, rural Senegal

**Trial Design**:

- An open-label randomised trial using the following regimens:

- Artesunate (one day) plus SP

- Artesunate (three days) plus SP

- Artesunate (three days) plus Amodiaquine (three days)

- Lapdap (three days)

Given at monthly intervals on three occasions

**Sample size:**

- 1680 children aged 1 to 6 years (420 for each of the four arms)

**Follow-up:**

- From July 2004 to January 2005, participants will be visited at least once a week by 10 field workers
- Mothers or guardians will be asked about any episode of illness during the past seven days
- Children who have fever or any other symptoms potentially related to malaria will be follow up for at least the three following days
- Clinical attacks of malaria will be documented and treated without charge in Niakhar’s health centres by three qualified nurses
- *dhfr*, *dhps* and *pfcrt* mutations will be monitored in parasites obtained during two cross-sectional survey before and after the interventions
- This study will identify the best suitable combination for sIPT taking into account the risk of selection of drug resistant parasites

**Ethical considerations:**

- Approval will be sought from the Ethics Review Board of the Senegalese Government and from the Ethics Committee of the London School of Hygiene and Tropical Medicine.
- Informed consent will be obtained from the parents or guardians before any child is included in the study.

**Short Title:**

- Efficacy, safety and impact on drug resistance of four sIPT regimens in rural Senegal.

**References**

# I. Aim

To improve control of malaria.

# II. General objective

To assess to what extent sIPT using these different drug regimens can prevent morbidity from malaria in rural Senegal.

# III. Specific Objectives

To compare the efficacy, safety and effect on drug resistance of artesunate (one day) plus SP, artesunate (three days) plus SP, artesunate (three days) plus amodiaquine and Lapdap when used for seasonal IPT in children.

# IV. Background/Rationale

**1**. **Malaria control in Sub-Saharan Africa**

In Sub-Saharan Africa, malaria remains the most common cause of morbidity and mortality. Mortality is estimated to cause over one million deaths a year. The vast majority of this loss of life occurs among young children, especially in remote rural areas of Africa (WHO 2000).

Although tremendous advances have been made in controlling the disease during the last two decades, malaria remains the major killer in sub-Saharan Africa. Community based trials with insecticide-treated bednets (ITN) , which started in the late 1980s in the Gambia and elsewhere, achieved a 40 to 60% short term-reduction in malaria mortality in children less than 5 years in areas with high coverage (Alonso, Lindsay et al. 1993; Greenwood and Pickering 1993). However, achieving high levels of coverage with ITN has proved difficult and other control strategies are needed.

Anti malarial chemoprophylaxis for the whole paediatric population has been shown to reduce malaria morbidity and all cause mortality but this strategy is not generally encouraged due to the threat of resistance and difficulties in implementation. Chemoprophylaxis can also result in loss of acquired immunity or a delay in the development of clinical immunity leading to a period of increased risk of clinical malaria on cessation of the intervention. Any new chemotherapeutic strategy should have the potential to prevent malaria infection without compromising the development of malaria immunity or encouraging drug resistance. Intermittent preventive treatment offers a potential way of achieving these objectives. Use of drugs in combination for IPT may help to prevent selection for resistance.

**2. Intermittent preventive treatment**

2.1. Definition

IPT can be defined as drug administration, in curative doses, given at specific opportunities (for example ante-natal visits or routine vaccinations), with the objective of preventing malaria. Drugs are provided irrespective of the presence of parasites or symptoms. Drugs used for IPT must be very safe as well as effective.

2.2 Intermittent preventive treatment in infants (IPTi)

The concept of IPT was initially developed for the control of malaria in pregnancy and the administration of SP on two occasions during the second and third trimesters of pregnancy is now recommended practice in areas of medium or high malaria risk (Parise, Ayisi et al. 1998; Shulman, Dorman et al. 1999). This approach was subsequently adapted to the prevention of malaria in Tanzanian infants (Schellenberg, Menendez et al. 2001) . Administration of SP on three occasions during the first year of life at the time of EPI vaccination was found highly effective. The rate of clinical malaria (events per person-year at risk) was 0.15 in the intervention arm versus 0.36 in the placebo group, giving a protective efficacy of 59% (95%CI 41-72). In 1999, Ib Bygbjerg and colleagues studied two hundred and ninety-one infants aged 12-16 weeks who attended Maternal and Child health clinics in a Tanzanian district where malaria is holoendemic (Ib C. Bygberg et al 2002). For a period of six months, these infants were given amodiaquine or placebo every 60 days. The authors showed that the protective efficacy of intermittent amodiaquine treatment in preventing malaria fevers was 64.7% (95% C.I. 42.4 to 77.2) p<0.001. Further studies of IPTi are underway in Kenya, Ghana, Mozambique, Mali and Gabon.

2.3 Intermittent preventive treatment in children (sIPT or IPTc)

The two studies conducted in Tanzania, where malaria transmission is intense and perennial have shown that IPT during infancy has the potential to become a major tool for malaria control in highly endemic parts of Africa. However, in many parts of Africa, especially those where transmission is seasonal, the main burden of malaria is in older children who would not be protected by an IPTi scheme which is limited to infants only. Except for impregnated bednets, there are no other efficacious tools available for preventing malaria in these children. Thus, we have explored the feasibility of using the IPT approach to prevent malaria in older children.

With support from the Gates Malaria Partnership, a study was undertaken in 2002 in children in Niakhar, a typical Soudano-Sahelian area of rural Senegal where malaria transmission is seasonal and intense. A single dose of SP plus one day of artesunate were given to 600 children in September, October and November, whilst 600 other children received a placebo. The incidence of clinical malaria was reduced by 86% in children who received the intervention.

Cross-sectional surveys were undertaken before and after the administration of sIPT. The prevalence of *Plasmodium falciparum* parasitaemia at the end of the malaria transmission season in children who had received the drug combination was 69% less than in the control children (11%% versus 35%). However, molecular studies showed that there had been a selection of parasites with *dhfr* mutations associated with pyrimethamine resistance in the children who had received SP plus artesunate but not in the control group. Although there was no overall increase in the number of resistant parasites in the children who had received sIPT, because the prevalence of infection was markedly reduced in these children, this finding is a matter of concern.

A single dose of artesunate has not been effective in preventing selection for parasites carrying genetic markers of SP resistance. Although the intervention reduces the absolute number of parasites with resistant genes to SP because of the lower carriage of parasites induced, there is significant selection for resistant genotypes in the IPT group. 95% of parasites in IPT recipients carried triple mutations in *pfdhfr* compared to 75% of parasites in the placebo recipients. (figure 1).

Figure 1: Prevalence of triple mutation before and after the intervention according to the randomisation groups ([name], [name]. & [name].; unpublished data).

Therefore, the other basis of this study is to investigate if other drug regimens might be equally effective in preventing malaria but more effective in preventing the emergence of resistant parasites. Thus, we now propose to compare the efficacy, safety and impact on drug resistance of four potential drugs regimens for sIPT. The drug combinations that we have selected for comparison are:

► Artesunate (one dose) + Sulfadoxine-Pyrimethamine

SP combinations with artesunate are now of limited use in East Africa where there is widespread resistance to SP but they may still being effective in West Africa where resistance to SP is less. Thus, we chose SP + one dose of artesunate as the combination of choice for the 2002 study in Niakhar in concordance with the WHO recommendation affirming that this is a suitable combination for IPT in infants (WHO 2001). A single dose of artesunate was used because this makes compliance easier and because there is little evidence that three doses are much more effective than one dose in eliminating gametocytes. For recall, with one dose of artesunate added to SP and given in September, October and November 2002, we reached a 86% reduction of clinical malaria incidence.

►. Artesunate (three doses) + Sulphadoxine-Pyrimethamine

SP combined with artesunate given for three days will be studied in order to determine if the administration of additional doses of artesunate will eliminate any potentially SP resistant parasites and thus prevent selection during the course of the sIPT administration.

►. Artesunate + amodiaquine

The efficacy and safety of this combination for the treatment of malaria has already been documented (Brasseur, Guiguemde et al. 1999) . Studies undertaken in East and West Africa have shown that the combination of artesunate and amodiaquine is an effective treatment and may be more effective at preventing late parasitological failure than the combination of SP and artesunate when some SP resistance is present (Dorsey, Njama et al. 2002). Thus, one might think that artesunate plus amodiaquine might be more effective than SP + one dose of artesunate in preventing selection of resistance during the course of sIPT.

According to a survey conducted in 1996 in Niakhar, Senegal , 16% of parasites were resistant to amodiaquine (Sokhna, Molez et al.).

►. Lapdap

Lapdap combines two anti folates (chlorproguanil and dapsone) which both have a short half-life. This should reduce the chance of selection of resistant parasites, especially when given in combination with artesunate. Lapdap is effective against parasites that are resistant to SP, and has been shown to be safe and effective when used to treat clinical malaria in African children.

There is less information on the combination of Lapdap with artesunate. Laboratory studies have shown no adverse interactions and a trial of the combination is currently under way in Malawi. Further studies of co-administration of Lapdap with artesunate will start in a number of African countries in 2004. A fixed combination is being developed by a GSK/MMV/WHO product development team. In this efficacy trial, Lapdap will is used alone as there are yet limited safety data on the Lapdap/artesunate combination.

# V. Hypothesis

Three doses of artesunate combined with SP or amodiaquine, and Lapdap used alone will be equally as effective at preventing malaria in young Senegalese children when used for sIPT as a regimen of SP combined with one dose of artesunate and less likely to select for resistant parasites

Two major endpoints will be considered in this study (i) the incidence of clinical malaria in children receiving one of these four interventions, (ii) the prevalence of parasites carrying genotypes associated with resistance following sIPT at the end of the transmission season.

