2.2. Exclusion criteria

Reasons for exclusion will include any of the following:

Any conditions causing an inability to take or retain oral medication.

Any chronic illnesses or severe conditions such as tuberculosis, epilepsy, obvious mental retardation or failure to thrive.

Severe congenital diseases such as heart malformations

Intake of an anti-malarial other than chloroquine within the previous two weeks

Known allergy to any of the antimalarial drugs used in the trial.

1. Study design

We will use an open label randomised trial comparing the following regimens:

- Artesunate one day plus SP

- Artesunate given for three days plus SP

- Artesunate plus Amodiaquine both given for three days

- Lapdap for three days

One of these combinations will be randomly allocated to all participants and given three times in early September, early October and early November 2004.

1. Sample size calculations

The trial is powered as an ‘equivalence’ or ‘negative’ trial, with the outcome being the cumulative incidence of malaria, ie the proportion of children having at least one episode of malaria during the course of the study. AS3+SP is the comparator and is expected to have cumulative incidence of 20%, and we aim to show that this is no more than 30% in the other three arms. To allow for three comparisons — AS3+SP compared with each of the other three arms — we set the significance level to 5/3% (≈0.0167%), one-sided. With 80% power, we need 336 children per arm (Jones, Jarvis et al. 1996). We expect no more than 20% to be lost to follow-up, which raises this to 420 per arm, or 1680 in total.

For the secondary drug resistance endpoint, this implies 336×0.2=67 cases on AS3+SP. To be conservative, we assume the same number on the other arms (if they turn out to be less effective than AS3+SP, this will only increase the power for this secondary endpoint). Among these cases, based on our previous study, we expect the prevalence of *dhfr* mutations at codons 108, 59 and 51 to be 90% in the AS1+SP arm. The 67 cases per arm then give us 77% power to detect a difference of 20% (ie 70% prevalence) in the other arms, with a significance level of 5% (two-sided, (Fleiss 1981)).

1. Enrolment procedure and follow-up

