At the time of the cross-sectional surveys filter paper blood samples will be collected and stored at 4 o C prior to analysis of molecular markers for resistance. For those children parasite-positive by microscopy, DNA will be extracted from the filter paper samples using standard techniques and amplified using PCR (Djimde, Doumbo et al. 2001). The reaction products will be probed for defined mutations in the dihydofolate reductase (*dhfr*), dihydroptypteroate (*dhps*) (Peterson, Di Santi et al. 1991) and *pfcrt* genes of *Plasmodium falciparum* using SSOP (Alloueche, Silveira et al. 2000). The prevalence of *dhfr* and *dhps* mutations associated with resistance to pyrimethamine will be compared between pre and post sIPT treatment samples in children who receive SP plus artesunate or Lapdap. Children who receive amodiaquine plus artesunate will act as controls. Similarly changes in the prevalence of *pfcrt* mutations before and after treatment will be measured in children who receive sIPT with amodiaquine plus artesunate whilst samples from children who receive SP or Lapdap will act as controls

1. Assessments of adverse events

Adverse events will be defined as any signs or symptoms, which first develop or increase in severity within seven days after intake. Any serious adverse events such as death or admission to hospital which occur within one week of drug administration will be thoroughly investigated and reported within 24 hours to the DSMB. To determine the prevalence of minor side effects following drug administration such as headache, fever, weakness, abdominal pain, anorexia, nausea, vomiting, diarrhoea, rash, itching or sleep disorder 100 randomly selected participants in each treatment group will be visited at home seven days after each round of drug administration and a side effects questionnaire completed. (*appendix 5*) Field staffs who complete these questionnaires will be unaware of the treatment group to which the child belongs.

1. Participants withdrawal

Parents will be at liberty to withdraw their children from the study at any time for any reason; this decision will not prejudice their children receiving malaria treatment.

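### The resistance power statement applies an SP marker (dhfr) to the artesunate-amodiaquine arm, which the protocol elsewhere uses as the unexposed control for that marker

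*Protocol*

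**What the plan says.** The Hypothesis section (Protocol V) covers three regimens: three-day artesunate plus SP (AS3+SP), AS+AQ and Lapdap. Each is expected to be as effective "as a regimen of SP combined with one dose of artesunate and less likely to select for resistant parasites". The matching endpoint is generic: "the prevalence of parasites carrying genotypes associated with resistance following sIPT at the end of the transmission season". No marker is named.

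The Sample size calculations section names one. From the 2002 study, "we expect the prevalence of *dhfr* mutations at codons 108, 59 and 51 to be 90% in the AS1+SP arm". It then states: "The 67 cases per arm then give us 77% power to detect a difference of 20% (ie 70% prevalence) in the other arms". The test is two-sided at 5%. The other arms are AS3+SP, AS+AQ and Lapdap.

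The section on assessment of resistance to antimalarials assigns markers by drug. dhfr and dhps are compared before and after treatment in the SP-artesunate and Lapdap children, and for that comparison "Children who receive amodiaquine plus artesunate will act as controls". pfcrt is compared before and after treatment in the AS+AQ children, with the SP and Lapdap children as controls.

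Section 13.3 repeats the dhfr planning assumption for AS3+SP against AS1+SP only. No section gives a pfcrt rate, target difference or power.

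**The concern.** The same arm has two incompatible roles for the same marker. In the power statement AS+AQ is a test arm, and lower dhfr prevalence is the sought result. In the resistance assessment section it is the arm without drug pressure on dhfr. A difference between AS1+SP and an arm that received no SP measures what SP does to dhfr. It carries no information on what amodiaquine selects.

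The study outline says the trial will identify the most suitable combination with the risk of selecting resistant parasites taken into account. If the powered contrast is read as the test of the hypothesis, AS+AQ could be credited with selecting less for resistant parasites on dhfr while pfcrt mutants rise in the same arm. The 77% would also be cited as the power of a claim it does not address.

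**Working it through.** **Inputs.** From Sample size calculations: 336 evaluable per arm, 20% cumulative incidence, dhfr 90% v 70%, 5% two-sided. From section IV.2.3: 2002 triple-mutant prevalence of 95% with AS1+SP and 75% with placebo. From section 13.3: a rise from about 50% to 90% on AS1+SP.

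**1. The plan's own figure.** 336 × 0.2 = 67.2, so 67 per arm. With the continuity correction,

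power = Φ{[d − 1/n − 1.96·√(2p̄(1−p̄)/n)] / √([p₁(1−p₁) + p₂(1−p₂)]/n)}.

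For n = 67, p₁ = 0.90, p₂ = 0.70: d = 0.20, p̄ = 0.80, null SE 0.0691, alternative SE 0.0669.
(0.20 − 0.0149 − 0.1355)/0.0669 = 0.742, so power is 77.1%. The stated 77% is right. Without the correction it is 83.3%.

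**2. What the dhfr contrast shows for AS+AQ.** Suppose AS+AQ has no effect on dhfr and sits at the 2002 placebo level of 75%.
- Against the 2002 AS1+SP level: 95 − 75 = 20 points, the size of the difference the trial is powered to detect. Power with 67 per arm is 86% (91% uncorrected).
- Against the planning value: 90 − 75 = 15 points. Null SE 0.0656, alternative SE 0.0644; (0.15 − 0.0149 − 0.1287)/0.0644 = 0.100, so power is 54% (63% uncorrected).
- If the unselected level were instead the 50% starting value in section 13.3, power against 90% would exceed 99%.

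So an arm with no SP pressure is expected to be lower on dhfr whatever amodiaquine does. The chance of a significant result depends on the background level.

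**3. What is available on pfcrt.** The protocol gives no rates, so a 20-point rise from a range of control levels is assumed, with 67 per arm. Power against a single control arm, same formula:

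| Control | AS+AQ | Corrected | Uncorrected |
|---|---|---|---|
| 40% | 60% | 57% | 64% |
| 50% | 70% | 59% | 66% |
| 60% | 80% | 65% | 72% |
| 70% | 90% | 77% | 83% |

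Pooling the three arms without amodiaquine gives 3 × 67 = 201 controls. The pooled p̄ is then weighted by arm size, the variance terms use 1/67 and 1/201, and the correction is ½(1/67 + 1/201) = 0.00995.
- 40% v 60%: (0.20 − 0.00995 − 1.96 × 0.0702)/0.0691 = 0.76, power 78%.
- 70% v 90%: (0.20 − 0.00995 − 1.96 × 0.0611)/0.0489 = 1.44, power 92%.

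Pooling assumes that the three control arms share one pfcrt prevalence.

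**4. Caveat on 67.** The 67 are clinical malaria cases, whereas genotyping is planned on parasite-positive survey samples. If December positivity were the 11% seen in treated children in 2002, 336 × 0.11 = 37 per arm. The single-arm pfcrt power would then be about 31–46% (continuity-corrected).

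**The case against.** The strongest reply is that the marker plan is already drug-specific. The resistance assessment section judges AS+AQ on pfcrt with the other arms as controls, so a rise in pfcrt mutants would be seen. The power sentence concerns an endpoint it calls secondary, and it uses the only marker with prior site data. Section 13.3 confines the assumption to AS3+SP v AS1+SP. The trial also exists because SP selects for pyrimethamine resistance, so removing that pressure is a real advantage. Much of this stands: pfcrt is planned, and the remedy is largely a matter of bringing the hypothesis and power statement into line with it. It does not remove the conflict. The hypothesis and endpoint speak of resistant parasites in general, and the one stated contrast and power are applied to an arm where they cannot support that claim.

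Two stronger readings are tempting, and the documents support neither.

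- A reader might infer that AS+AQ wins by construction. The direction is favoured, but significance is not assured: power is 54% at 75% v 90%.
- A reader might infer from "Lapdap is effective against parasites that are resistant to SP" that selection by Lapdap goes unmeasured. The same section describes Lapdap as two antifolates, and a before-and-after dhfr/dhps comparison is planned in Lapdap children with AS+AQ as controls. Activity against mutant parasites does not exclude selecting for them. Nothing in the protocol says that these genes fail to reflect Lapdap pressure.

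**Conclusion.** The point holds for AS+AQ only. The 77% is arithmetically correct, but for that arm it is attached to a contrast that cannot test the hypothesis and that conflicts with the arm's control role. The 2002 figures put the expected dhfr gap from absence of SP alone at 15 to 20 points (75% against 90% or 95%), compared with a 20-point target. The arm's own marker has no stated precision. Under assumed 20-point rises from 40–70%, power is about 57–77% against one arm and 78–92% against the three pooled.

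This rests on two assumptions: that the 2002 placebo level approximates dhfr prevalence without SP pressure, and that 67 genotyped samples per arm are obtained. The AS3+SP and Lapdap contrasts with AS1+SP are not affected.

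**What to change.** 1. **Sample size calculations:** limit the 90% v 70% dhfr contrast and the 77% to AS3+SP and Lapdap, each against AS1+SP.
2. **Assessment of resistance and section 13.3:** assess selection by AS+AQ on December pfcrt prevalence against the three arms without amodiaquine. Report the difference with a confidence interval, and state that a non-significant result is not proof of no selection. Give the assumed pfcrt rates and the resulting precision.
3. **Hypothesis:** tie the claim of less selection to the marker of each regimen's own partner drug. Describe any dhfr advantage of AS+AQ only as absence of SP-marker selection.

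The cost is wording. All three genes are already to be typed, and every arm already serves as test or control. The downside is a narrower resistance claim for AS+AQ, and a less well powered one if it is compared with single arms rather than with the three pooled.
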